### Eligibility Criteria: Exclusion Criteria

Patients with the following characteristics will be excluded from the trial:
(a)Severe dementia, identified by implementing the MMSE (22).(b)History of an organic disorder or major psychiatric impairment (20).(c)Other comorbid disease or disability such as cancer or amputation that will prevent or limit assessment of the patients and their, participation or follow-up over a period of 20 weeks (20, 23).(d)Positive Dix–Hallpike test (to exclude BPPV of posterior and anterior SCCs).Because the Dix–Hallpike test and CRT (Epley) maneuver require the head rotation of 45° and the extension of 20° to 30°, patients with a history of neck surgery, recent neck trauma, severe rheumatoid arthritis, atlanto-axial and occipito-atlantal instability, cervical myelopathy or radiculopathy, carotid sinus syncope, Chiari malformation, and vascular dissection syndromes will be excluded from the study (24).(e)Positive Roll test (to exclude BPPV of horizontal SCCs).(f)Participation in other pharmacological or rehabilitation intervention studies which can confound the results of this study (20).

In phase 2 of the study, the same inclusion/exclusion criteria will be applicable as in phase 1 since patients will be randomly recruited from patients assessed in phase 1 of the study.

### Sample Size

The sample size of phases 1 and 2 are interrelated and was calculated simultaneously with the assistance of a statistician. All patients who suffered a stroke and will be admitted at one of the pre-selected rehabilitation hospitals in Pretoria and Johannesburg, Gauteng for rehabilitation in the sub-acute phase will be assessed to determine if they meet the inclusion and exclusion criteria of the study. Recruitment and assessment of patients will be done in each of the rehabilitation centers in a consecutive sequence based on the number of patients in a particular center at a given time until an adequate and representative sample group (*n* = 100) for the trial has been reached. An adequate and representative sample size required for phase 1 of the study was calculated based on a relatively small, but similar study (12). These authors reported the geometric mean and 95% confidence interval (CI) at baseline and the end of each week of the treatment period. The expected geometric mean of the Barthel Index value at onset was 45 (12) and an improvement in the change from baseline at 2 weeks for the combination of VSE integrated with task-specific activities group (experimental group) compared with the task-specific activities group (control group) is 36 which is 0.214 on the logarithmic (base 10) scale. From the reported 95% CI for the geometric mean, a SD of 0.179 on the log scale was calculated. Since a change from baseline of interest, this SD was inflated by a factor (√2 to 0.249). Based on this information, a sample of at least 30 patients per group will have 90% power to detect the clinical relevant change when testing at the 0.05 level of significance. If testing was one-sided (VRT, VSE, and task-specific activities), based on the published results of the previous study (12), a sample of 30 patients per group will be required. Hence, to achieve a sample size of 30 patients per group, the cross-sectional part of the study (phase 1) will need to enrol at least 100 patients in the sub-acute phase. Prevalence of visual impairments and central vestibular dysfunction will be of interest. As the latter is expected to be in excess of 70% the above sample size is adequate to estimate the prevalence’s to an accuracy within 10%. One hundred patients who meet the eligibility criteria and will give written informed consent to participate in the study will therefore be included in phase 1 of the trial.

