### Data Management and Analysis

Data of the cross-sectional survey (phase 1 of the study) will be analyzed and reported according to the STROBE checklist. Data of the cross-sectional clinical trial (phase 2 of the study) will be analyzed and reported according to the CONSORT statement. The outcomes measures measuring the clinical outcomes the data summary will make use of descriptive statistics, geometric mean, SD, median, range, and 95% CIs will be used when data conforms to a Gaussian distribution. Results from the two groups will be compared with respect to outcome at 2 weeks, adjusted for baseline values, using analysis of covariance (ANCOVA), using ranks when data are skewed. Data characteristics permitting, groups may also be compared using a mixed-model approach which will indicate the data over all the time points where treatment, time, and treatment–time interaction will be entered into the model, and the treatment–time interaction will be of primary intent. Testing will be done at the 0.05 level of significance.

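### The 30 per group reproduces only as a two-sided 0.05 test; the one-sided figure and the inflated SD are wrong, and the step from 36 to 0.214 cannot be traced

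*Protocol article*

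**What the plan says.** The Sample Size section takes its inputs from an earlier, similar trial. For the baseline it says: "The expected geometric mean of the Barthel Index value at onset was 45". The between-group improvement in change from baseline at 2 weeks "is 36 which is 0.214 on the logarithmic (base 10) scale". An SD of 0.179 on the log scale is derived from a reported confidence interval, and because change from baseline is of interest "this SD was inflated by a factor (√2 to 0.249".

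From these inputs it concludes that "a sample of at least 30 patients per group will have 90% power to detect the clinical relevant change" at the 0.05 level, without naming the sides of the test. The next sentence opens "If testing was one-sided (VRT, VSE, and task-specific activities" and ends by saying that "a sample of 30 patients per group will be required".

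The Data Management and Analysis section plans an ANCOVA of the 2-week outcome adjusted for baseline, on ranks if the data are skewed, with a mixed model as an option. On the error rate it says only: "Testing will be done at the 0.05 level of significance".

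**The concern.** One set of inputs cannot give the same sample size for a two-sided and a one-sided test at the same level and power. By giving 30 for both, the section leaves open which test the trial was sized for, and the analysis section does not settle it. The abstract makes the training of rehabilitation staff depend on a Barthel result that is clinically and statistically significantly better in the experimental group, so the sidedness bears on the decision that the trial is meant to support.

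Two of the inputs also look wrong or cannot be followed. The inflated SD is not √2 times the SD given just before it. The figure of 36, which has no unit, does not become 0.214 on the log10 scale by any direct use of the baseline of 45. Since 0.214 is what the section treats as the clinically relevant change, a reader should be able to see what it means on the Barthel scale.

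**Working it through.** **Inputs, all from the Sample Size section:** effect δ = 0.214 and SD σ = 0.249 (both log10), single-time SD 0.179, baseline geometric mean 45, level 0.05, power 90%, 30 per group, 1:1 allocation.

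**1. The plan's own figure.** Normal approximation: n = 2(z_α + z_β)²(σ/δ)² per group, with (0.249/0.214)² = 1.354.

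- Two-sided 0.05: 2 × (1.960 + 1.282)² × 1.354 = 28.5, so 29. The noncentral t calculation gives 29.45, so 30. Power at 30 per group is 90.5% (t) or 91.4% (normal).
- The stated 30 per group and 90% power are therefore reproduced, as a two-sided test.

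**2. The one-sided sentence.** Same inputs, one-sided 0.05: 2 × (1.645 + 1.282)² × 1.354 = 23.2, so 24. The t calculation gives 23.90, also 24. Power at 30 per group is 95.0% (t) or 95.4% (normal). The stated requirement of 30 is not reproduced.

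**3. The inflated SD.** √2 × 0.179 = 0.2531. Rounding of 0.179 does not explain 0.249: √2 × 0.1785 = 0.2524 and √2 × 0.1795 = 0.2539. Working backwards, 0.249/√2 = 0.176. The stated value is about 1.6% too small (0.249/0.2531 = 0.984).

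| SD | Test at 0.05 | n per group for 90% (t) | Power at 30 per group (t) |
|---|---|---|---|
| 0.249 (as stated) | two-sided | 29.45, so 30 | 90.5% |
| 0.249 (as stated) | one-sided | 23.90, so 24 | 95.0% |
| 0.253 (√2 × 0.179) | two-sided | 30.40, so 31 | 89.6% |
| 0.253 (√2 × 0.179) | one-sided | 24.67, so 25 | 94.4% |

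By the normal approximation, SD 0.253 gives 30 per group and 90.6% power two-sided.

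**4. From 36 to 0.214.** Back-transforming, 10^0.214 = 1.637. Applied to 45 this gives 73.7, a gain of 28.7 and not 36. Direct readings of 36 do not give 0.214 either:

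- a gain of 36 points on 45: log10(81/45) = 0.255;
- a 36% increase: log10(1.36) = 0.134.

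The figure can be reached with group values that the article does not state:

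- A 36-point difference between groups has ratio 1.637 if the control value is 36/0.637 = 56.5 and the experimental value 92.5.
- An experimental gain of 36 (45 to 81) against a control value of 49.5 also gives log10(81/49.5) = 0.214.

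These pairs are assumptions. They show that the conversion depends on the 2-week values in each group.

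**The case against.** The strongest reply is that the calculation used for the trial is sound: 0.214, 0.249 and a two-sided 0.05 test give 30 per group at 90% power. An unqualified 0.05 level is ordinarily read as two-sided, the one-sided sentence is conditional, and an article may leave the sidedness of the analysis to the full protocol or SAP. Most of this stands. A reader might infer that the 90% power has no basis, but step 1 shows that it does. The analysis section's silence on sides would not be a finding alone. It matters here because the Sample Size section brings in a one-sided test and gives it a wrong number. That 30 would fit a one-sided test at 0.025, which is the two-sided calculation again, but the section names only 0.05.

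It may also be said that the SD slip is immaterial. For the sample size it is: power moves by about one percentage point. It is still an incorrect figure.

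Three stronger readings are tempting, and the article does not support them.

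- **That 36 is shown not to equal 0.214, so that true power could be far from 90%.** The article powers directly on 0.214, attaches no percent sign to 36, and describes a between-group difference whose conversion needs values it does not give. The step is untraceable, not disproved.
- **That the phase 1 total of 100 rests only on this calculation.** The section also justifies 100 by the precision of a prevalence above 70% to within 10%, and this checks: 1.96 × √(0.7 × 0.3/100) = 0.090.
- **That the planned ANCOVA has a residual SD of at most 0.179, so the trial is heavily overpowered.** This needs the baseline and 2-week SDs to be equal, which the article does not say. If they are similar, sizing on an uncorrelated change score is conservative for ANCOVA. That is a common choice and not an error.

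**Conclusion.** The Sample Size section is wrong as written in two figures and unclear in a third; the planned number per group stands.

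- The one-sided requirement of 30 per group is wrong. It should be 24 with the stated SD or 25 with the corrected one, and 30 per group gives about 94–95% one-sided power.
- The inflated SD should be 0.253 if 0.179 is right. Two-sided power at 30 per group is then 89.6%, and 31 per group would be needed to reach 90% by the t-test.
- The origin of 0.214 cannot be followed. The one firm statement is that it is a between-group ratio of about 1.64.

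These results assume a two-sample comparison of mean log10 change with equal group sizes. Severity is minor to moderate: the size of the trial is not in doubt, but the sidedness of the test behind its decision should be fixed before results are seen.

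**What to change.** Keep 30 per group and rewrite the paragraph:

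1. State a two-sided 0.05 test in both the Sample Size and the Data Management and Analysis sections, and delete the one-sided sentence.
2. Correct the inflated SD to 0.253 and the power to about 89.6%. If the original calculation shows that 0.179 is the misprint, correct that value instead (0.249/√2 = 0.176); the power then stays at 90.5%.
3. Give the control and experimental 2-week Barthel values behind 0.214, or state the effect as a ratio of 1.64, and say what 36 measures and in what unit.
4. Optionally, add that sizing on an uncorrelated change score is conservative for the planned ANCOVA if the baseline and 2-week SDs are similar.

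The cost is a few sentences in two sections, with no change to enrolment, visits or assessments.

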#### Cross-Sectional Clinical Trial: Phase 2 of the Study

Patients with or without visual impairment and/or vestibular dysfunction will be identified based on the results of patients’ diagnosis after the battery of standardized outcome measures has been completed by two independent assessors (audiologist and physiotherapist) during phase 1 of the study. Sixty patients with (visual and/or vestibular dysfunction) identified in phase 1 of the study will be recruited to participate in the second phase of the study and randomly allocated to either Group 1 or Group 2. The study population will include the data of the first 30 patients in each group who participate in the study for all 20 weeks. The two groups of 30 patients in the respective group do not make provision for drop out of participants in the study. If patients leave the study for any reason, they will have to be replaced by another patient. The results of this first battery of tests (phase 1) will serve as the baseline measurements for phase 2 of the study. In phase 2, the researcher will determine the effect of the combination of VRT and VSE integrated with task-specific activities (*n* = 30) as an intervention approach for patients in the sub-acute phase post-stroke compared with patients who will receive task-specific activities (*n* = 30) alone as an intervention approach on their: (a) visual impairments, (b) central vestibular dysfunction, (c) cognitive function, (d) residual oculomotor visual performance, (e) visual–perceptual system, (f) functional balance, (g) ability to modify gait in response to changing task demands, (h) functional ability, and (i) presence of anxiety and/or depression after the intervention period of 2 weeks. The consecutive assessment will be repeated by the two independent assessors after the 2-week intervention period. Twenty weeks after rehabilitation has been terminated, the physiotherapist (independent assessor) will contact all patients who completed phase 2 of the study, to complete the Telephonic-Administered International Physical Activity Questionnaire (IPAQ). The aim will be to determine the effect of the combination of VRT and VSE integrated with task-specific activities for patients in Group 1 (experimental group), compared with patients who will receive task-specific activities alone Group 2 (control group) on patients’ participation activities 20 weeks after rehabilitation has been terminated.

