Patients will receive intervention daily for a period of 2 weeks. The period of intervention consisting of 2 weeks was selected due to the fact that patients are on average admitted to a private rehabilitation setting post-stroke for a period of 2 weeks. The intervention period of 2 weeks were further decided upon because results from a previous study (12) demonstrated a statistically significant (*p* = 0.02) difference between Group 1 and Group 2 after 2 weeks intervention (12). Any adverse effects within the period of 20 weeks will be documented.

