#### Limitations of the Study

•Upon completion of the previous study by the authors, a large number of drop out of participants after discharge from various rehabilitation settings in South Africa was observed limited long-term follow-up despite the fact that participants received remuneration for traveling costs and were contacted telephonically on a regular basis. The large loss to follow-up prevented the researcher from determining whether the long-term effect of the treatment was sustained and was regarded as a limitation of the previous study.•Twenty weeks after rehabilitation has been terminated, the physiotherapist (independent assessor) will contact all patients who completed phase 2 of the study, to complete the Telephonic-Administered International Physical Activity Questionnaire (IPAQ) to determine the effect of the combination of VRT and VSE integrated with task-specific activities for patients in Group 1 (experimental group), compared with patients in Group 2 (control group) who will receive task-specific activities alone on their participation activities 20 weeks after rehabilitation has been terminated.

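### Thirty patients per group followed for 20 weeks is not assured: phase 1 stops at 100, nothing is allowed for drop-out, and late losses cannot reliably be replaced

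*Protocol article*

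**What the plan says.** **Size of phase 1.** The Sample Size section derives 30 patients per group for phase 2. It says that phase 1 "will need to enrol at least 100 patients in the sub-acute phase", recruits until 100 is reached, and closes with the same number for that phase: "One hundred patients who meet the eligibility criteria and will give written informed consent to participate in the study will therefore be included in phase". The phase 1 data collection section repeats the figure of 100.

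**Share expected to qualify.** Of prevalence, the Sample Size section says: "As the latter is expected to be in excess of 70" per cent.

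**Source of phase 2 patients.** "Sixty patients with (visual and/or vestibular dysfunction) identified in phase 1 of the study will be recruited to participate in the second phase". The Exclusion Criteria section likewise takes phase 2 patients from those assessed in phase 1. The phase 1 battery is the phase 2 baseline.

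**Loss.** The phase 2 section states: "The two groups of 30 patients in the respective group do not make provision for drop out of participants in the study". Anyone who leaves, for whatever reason, is to be replaced. The study population is the first 30 in each group who take part for the full 20 weeks.

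**Timing.** Treatment lasts 2 weeks, chosen partly because "patients are on average admitted to a private rehabilitation setting post-stroke for a period of 2 weeks". The telephone questionnaire (IPAQ) follows 20 weeks after rehabilitation ends.

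**Past experience.** The Limitations section reports, for the previous study, "a large number of drop out of participants after discharge", and says that this prevented assessment of the long-term effect.

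**The concern.** Each rule is reasonable alone, but together they leave little room. The only source of replacements is a pool that stops at 100, and the number to be reached is counted in 20-week completers. A replacement is useful only if that person has a recent baseline and is still available for daily inpatient treatment. For a patient lost at the final call, those conditions are hard to meet.

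If losses exceed the spare patients, or come too late to replace, the site has three choices: enrol beyond 100, treat replacements against old baselines, or finish with fewer than 30 per group. Because the study population is limited to 20-week completers, a shortfall at the telephone call also removes patients from the 2-week Barthel Index comparison, on which the power calculation rests.

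**Working it through.** **1. The plan's own figure.** Inputs from the Sample Size section: difference 0.214 and SD of change 0.249 on the log10 scale, 5% level, 90% power. The standardised difference is 0.214/0.249 = 0.859. A two-sided t-test needs 30 per group, with power 90.5%. The 30 per group is reproduced, so phase 2 needs 60.

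**2. Phase 1 with no loss.** 60/0.70 = 85.7, so 86 patients. One hundred is enough to start 60: the chance that at least 60 of 100 qualify at 70% is 98.8%. The question is what remains for loss.

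**3. Spare patients and tolerable loss.** Spare = 100 × q − 60. Tolerable loss = 1 − 60/(100 × q), where q is the qualifying share and loss covers refusal and drop-out together.

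| q | Qualify | Spare | Tolerable loss |
|---|---|---|---|
| 70% (stated floor) | 70 | 10 | 14.3% |
| 80% (assumed) | 80 | 20 | 25% |
| 91% (assumed) | 91 | 31 | 34% |

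The 91% supposes that visual impairment and central vestibular dysfunction each occur in 70% and are independent: 1 − 0.3 × 0.3 = 0.91.

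**4. Chance of at least 60 completers from 100.** X ~ Binomial(100, q × (1 − loss)), P(X ≥ 60). The protocol gives no loss rate, so these are assumed.

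| Loss | q = 70% | q = 80% | q = 91% |
|---|---|---|---|
| 10% | 77% | 99.7% | >99.9% |
| 14.3% | 54% | 97% | >99.9% |
| 20% | 24% | 83% | 99.8% |
| 30% | 2% | 24% | 81% |

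This is a best case for the plan. It counts every qualifying patient as usable and asks only for 60 in total, not 30 in each group. If 60 are started and no usable replacement exists, 10% loss leaves 54 and 20% leaves 48.

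**5. Timing.** If rehabilitation ends with the 2-week intervention, the call falls at 2 + 20 = 22 weeks after baseline. An unallocated phase 1 patient assessed at about the same time would by then have a baseline some 22 weeks old and, on the stated average stay, would have left about 20 weeks before.

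**6. Randomising all who qualify at the 70% floor.** About 70, or 35 per group. Expected at 2 weeks with 14.3% loss: 35 × 0.857 = 30. This is a mean: the chance that both groups keep at least 30 of 35 is about 38% (about 75% at 10% loss). Expected at 20 weeks: 35 × 0.80 = 28 and 35 × 0.70 = 24.5.

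**The case against.** The strongest reply is that 70% is a floor. Phase 2 admits patients with visual impairment, central vestibular dysfunction, or both, and the share with either condition cannot be lower than the share with one. If 80 to 91% qualify, the chance of 60 completers at 20% loss is 83 to 99.8%. This stands: 10 spares is the lowest figure consistent with the plan, not its expected one. It does not settle the matter, because neither the qualifying share nor the loss is stated more closely, and at 80% qualifying a 30% loss brings the chance down to 24%.

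Second, a reader might infer that phase 1 is rigidly capped and that every spare patient will have gone home. The protocol does not support that. It also speaks of at least 100. The 2-week stay is given for private settings only, while public ones also take part. Centres are worked through in sequence at about 4 weeks each, and their number is not given, so a later centre could replace some early losses. It could not do so for the last patients enrolled.

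Third, the 20-week contact is only a telephone call, which may lose fewer patients than visits would. That is fair, but the previous study lost many despite regular telephone contact and paid travel.

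Fourth, the 90% power concerns the 2-week Barthel Index, and none is claimed for the 20-week questionnaire. That is correct. Later loss reaches the powered comparison only through the restriction to 20-week completers.

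**Conclusion.** The concern holds in a limited form: 30 per group at 20 weeks is not assured, and replacing a patient lost at the final call is not workable as written. One might go further and say that the number will not be delivered. The protocol does not support that, because the answer depends on a qualifying share known only to exceed 70% and on a loss rate that is not stated.

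At the 70% floor the margin is 10 patients, or 14% loss including refusals. It rises to 25% at 80% qualifying and about 34% at 91%. Planning with no allowance sits badly with the large loss reported for the previous study. If 24 per group remained in the completers-only population, power for the 2-week comparison would be about 83% on the plan's inputs (two-sided t-test), against 90.5% with 30.

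**What to change.** - Randomise every qualifying, consenting phase 1 patient when assessed, instead of holding some back. At the 70% floor this is about 70 patients, roughly 35 per group.
- In the phase 2 section, delete both the replacement rule and the sentence limiting the study population to the first 30 per group who complete 20 weeks. Removing only the first would leave the analysed set dependent on 20-week loss.
- Analyse the 2-week outcomes in all randomised patients with 2-week data, whatever their 20-week status.
- Restate the Sample Size and phase 2 sections as about 35 randomised per group; an expected, not guaranteed, 30 per group at 2 weeks if loss is about 14%; and an expected 24 to 28 per group for the 20-week questionnaire under an assumed 20 to 30% loss.

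The cost is wording in two sections, about 5 more patients treated per group (more if the qualifying share exceeds 70%), and a less favourable stated number at 20 weeks. Phase 1 is not enlarged.
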